### Sample size considerations and calculations

The sample size is calculated to guarantee a certain precision of a range of estimates, not to achieve a certain power to detect an *a priori* defined effect size.

With 500 eligible cases in either cohort, this study fulfils the following prerequisites:

1. 95% confidence intervals of both risk and mean differences must not exceed the point estimate by more than 5% in either direction

2. multivariate modelling must be possible for five independent covariates (respecting Harrell’s rule)

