## Methods/Design

### Design

The Dose Reduction in whole-body computed tomography of Multiple Injuries (DoReMI) investigation is a prospective cohort study employing two large, consecutive cohorts of patients undergoing different approved and established MDCT protocols. All data will be recorded, stored and processed under the conditions of daily practice of trauma care. Gathered data will form the basis for a later interrupted time-series comparison between the effectiveness and safety of the scanning protocols.

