Consequently, the investigators changed their approach to comply with the IRB’s recommendations, and consented on a before/after cohort study. All patients in this study will receive an accepted diagnostic standard of care using approved technologies but will not undergo random allocation to either modality. One may still argue that injuries are acute, unforeseeable events, and there remains a random component in the study set-up.

The ultimate consequence of shifting from an experimental to an observational design was the increase in the sample size to allow for robust multivariate modelling and adjustment of results for confounding.

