### Primary outcome

Delayed diagnoses comprise pathological anatomic and / or physiologic findings which demand clinical awareness, or, in case of therapeutically relevant pathological results, should prompt immediate therapeutic action.

We will estimate the incidence of delayed diagnoses based on a synopsis of all subsequent clinical, imaging, intra-operative, and autopsy findings until discharge. We will further distinguish between clinically relevant and all diagnoses. Relevant diagnoses are defined as severe injuries suiting an Abbreviated Injury Scale [AIS] score ≥3 and/or injuries demanding surgical and/or trans-vascular intervention. Non-traumatic incidental findings like tumours or tumour-like lesions demanding specific work-up and/or treatment will be recorded in an exploratory attempt.

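### At 500 per cohort the stated 5% bound on confidence intervals fails if relative to the estimate, and if absolute holds only for risks of about 20% or less (or 80% or more)

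*Protocol article*

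**What the plan says.** The section on sample size considerations in the protocol article bases the number on precision and disclaims power: "The sample size is calculated to guarantee a certain precision of a range of estimates, not to achieve a certain power". It continues "With 500 eligible cases in either cohort, this study fulfils the following prerequisites", and lists two. The first is "95% confidence intervals of both risk and mean differences must not exceed the point estimate by more than 5% in either direction". The second is "multivariate modelling must be possible for five independent covariates (respecting Harrell’s rule").

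The section on design history gives a related reason for moving to a larger study, namely the "increase in the sample size to allow for robust multivariate modelling and adjustment of results for confounding".

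The primary outcome is a proportion: "We will estimate the incidence of delayed diagnoses based on a synopsis of all subsequent clinical, imaging, intra-operative, and autopsy findings until discharge". The article gives no expected value for it. The Design section looks ahead to the main comparison: "Gathered data will form the basis for a later interrupted time-series comparison between the effectiveness and safety of the scanning protocols".

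**The concern.** The first prerequisite is a checkable property of the design, and the article asserts it without conditions. It does not say whether 5% is a fraction of the estimate or an absolute amount, and it shows no calculation leading to 500. The width of an interval for a risk difference depends on the underlying risks, so one number of patients cannot fix it for every outcome.

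What is at stake is how a finding of no difference is read. The review board's worry was missed injuries under the lower dose, and the Discussion hopes for nearly confirmatory conclusions. A reader who takes the bound as given may credit the comparison of delayed diagnoses with more precision than it has.

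**Working it through.** **Inputs from the article.** n = 500 per cohort (sample-size section). VAS SD of 4 mm (design history). Pilot mean differences and SDs (Table 2): organ 3.62 mm with SDs 3.92 and 7.87; lung 0.60 mm with SDs 1.89 and 2.03. **Assumed, because the article gives none:** the risks, shown over a range.

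**The plan's own figures.** No calculation is shown for 500, so there is none to reproduce. The figure for the abandoned randomised trial does reproduce: 2 × 4² × (1.96 + 0.84)² / 1² gives about 251 to 252 per group, against the stated 253. The issue is therefore confined to the precision statement.

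**Formulas (Wald 95% half-widths).**
- Mean difference: 1.96 × √((s₁² + s₂²)/n)
- Risk difference: 1.96 × √((p₁(1−p₁) + p₂(1−p₂))/n)

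**Reading 1: 5% of the estimate, as literally worded.**
- Organ: 1.96 × √((3.92² + 7.87²)/500) = 0.771 mm; 0.771/3.62 = 21%.
- Lung: 1.96 × √((1.89² + 2.03²)/500) = 0.243 mm; 0.243/0.60 = 41%.
- The other three tissues fall between: fluid/fat 22%, vessel 30%, bone 33%.
- Bringing these to 5% would take about 9,065 (organ) to 32,836 (lung) patients per cohort.
- Risks of 10% and 15% (assumed): 1.96 × √((0.09 + 0.1275)/500) = 4.09 points, which is 82% of the 5-point difference. About 133,700 per cohort would be needed.
- Other assumed pairs: 10% and 5% give 65%; 20% and 10% give 44%. An extreme pair such as 90% and 10% does meet the bound (4.6%).
- For means with equal SDs the half-width is 1.96 × √(2/500) = 0.124 SD. The bound then needs a difference of at least 0.124/0.05 = 2.48 SD, or 9.9 mm at SD 4 mm.
- As the true difference approaches zero, 5% of it also approaches zero and no sample size suffices.

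**Reading 2: 5 percentage points, or 5 mm on the VAS.** With equal risks in the two cohorts:

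| Risk in both cohorts | Half-width at 500 per cohort (points) | n per cohort for 5 points |
|---|---|---|
| 5% | 2.7 | 146 |
| 10% | 3.7 | 277 |
| 20% | 5.0 (4.96) | 492 |
| 30% | 5.7 | 646 |
| 50% | 6.2 | 769 |

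Setting 1.96 × √(2p(1−p)/500) = 0.05 gives p(1−p) = 0.163, so p = 20.5% or 79.5%. Between these values the bound is missed. For the VAS, 1.96 × 4 × √(2/500) = 0.50 mm, and at the largest pilot SD (7.87 mm) 0.98 mm; both are well inside 5 mm.

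**Where 5 points would hold without conditions.** For one cohort's own proportion the worst case is 1.96 × √(0.25/500) = 4.4 points. The text, however, speaks of differences.

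**Illustration only: adjustment for time.** Suppose 1,000 evenly ordered patients and a model with a step at patient 500 plus a linear trend. The squared correlation between the step indicator and order is (1/8)² / ((1/4)(1/12)) = 0.75. The variance of the step effect is multiplied by 1/(1 − 0.75) = 4 and its half-width by 2, for example from 3.7 to 7.4 points at 10% incidence. The article does not specify this model.

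**The case against.** The strongest reply is that 5 percentage points was meant. Then 500 per cohort is close to the right number for risks of about 20% (492), and it is more than enough at 5% or 10%. On a 100-mm VAS, 5% reads naturally as 5 mm, which is met about ten-fold at SD 4 mm. The assumed incidence may stand in the full protocol, which is not shown, and its absence from a condensed article is not a fault. The analysis plan will report actual 95% intervals, so the achieved precision will be visible, and the Discussion concedes that the design cannot give formal proof. No decision rule uses the 5% sentence.

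Most of this stands. It limits the consequence, and it means that failure for the primary outcome is not shown. It does not rescue an unconditional claim covering risk differences in general.

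Three stronger readings are tempting, and the documents do not support them:
- A reader might infer that 500 has lost its only justification. The same section lists the five-covariate rule, and the design history cites modelling and confounding adjustment.
- A reader might infer that the time-adjusted analysis will have twice the width. The article names an interrupted time series and generalised linear, random- and mixed-effects models, but fixes no step-plus-linear-trend form. The 5% criterion itself concerns plain differences.
- A reader might put a figure on the width for sensitivity. That needs the number of injured patients and the sensitivity itself, and the article gives neither.

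**Conclusion.** The precision statement is wrong as written. On the literal reading it fails by a factor of about four to eight on the protocol's own pilot figures (21% to 41% against 5%), and by more for the assumed risk pair of 10% and 15%. On the absolute reading it is conditional: correct for a crude risk difference when both risks are about 20% or less (or 80% or more), and missed by up to 1.2 points in between (6.2 against 5). For the VAS the absolute bound is easily met.

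Whether it holds for the crude comparison of delayed diagnoses depends on an incidence that the article does not give, so it can be neither confirmed nor ruled out. All the widths above are unadjusted Wald intervals with every patient contributing. Nothing here shows that 500 per cohort is too few for the study's descriptive aims. The defect is a design property claimed without the conditions on which it depends.

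**What to change.** Keep 500 per cohort, remove the word guarantee, and replace the first prerequisite with an absolute statement, for example:

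*With 500 patients per cohort, the half-width of the 95% confidence interval for an unadjusted risk difference is at most 5 percentage points when the risk is 20% or less in both cohorts, and up to 6.2 points otherwise. For a mean difference on the 100-mm VAS it is about 0.5 mm at an SD of 4 mm and about 1.0 mm at an SD of 7.9 mm. Contrasts adjusted for time will be wider, as will differences in sensitivity, which rest only on patients with the injury.*

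If an expected incidence of delayed diagnoses is available, state it with its half-width from the table above. A note that a step plus linear time trend would about double the half-width may be added as an illustration, provided it is not presented as the chosen model. Leave the five-covariate prerequisite as the second stated reason.

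The cost is a few sentences and a less favourable precision claim. No extra patients, no change of outcome and no change of analysis are needed.

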### Analysis plan

Accepted statistical methods will be used to determine whether the distribution of baseline variables and outcome results are compatible with chance. In general, results will be presented as means, medians, or proportions, and differences in means and proportions, including appropriate measures of distribution and 95% confidence intervals.

We will use established methods to model observational, specifically time-series data, stratified for the different imaging protocols and potential confounding, independent variables. This will include multi-variable generalized linear, random- and mixed-effects regression analyses.

Missing values will be addressed by adequate methods (including multiple imputation techniques).

Multivariate modelling will always be conducted using sound selection, entry, and exclusion of variables, and after testing for model fit and plausibility.

EQUATOR-, GCP-, GEP-, and AMA-conformity will be assured when presenting results. Raw numbers and counts will be provided together with percentages. The STATA 11.0 software package will be employed for all analyses.

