## Abstract

**Background:**

Single-pass, contrast-enhanced whole body multidetector computed tomography (MDCT) emerged as the diagnostic standard for evaluating patients with major trauma. Modern iterative image algorithms showed high image quality at a much lower radiation dose in the non-trauma setting. This study aims at investigating whether the radiation dose can safely be reduced in trauma patients without compromising the diagnostic accuracy and image quality.

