## Discussion

This is the first study which assesses the potential value of a dose-reducing MDCT regimen in patients with multiple and severe trauma. The investigators initially planned a RCT which was rejected by the local IRB.

The current protocol aims at balancing regulatory and methodological issues. While the present study (because of its non-experimental design) cannot formally prove that low-dose MDCT is feasible, safe, and evenly accurate compared to normal-dose MDCT in the trauma setting, the cohort size, the setting, and the anticipated characteristics of patient cohorts will guarantee both high internal and external validity of findings. Advanced statistical approaches will allow for quasi-confirmatory inferences. In the absence of large-scales RCTs, this study may provide the best available evidence to decide in favour of one or the other diagnostic approach.

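### The aim is to show no harm, but outcomes are checked only against chance and no tolerable increase in delayed diagnoses is set for reading the confidence intervals

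*Protocol article*

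**What the plan says.** The Abstract (Background) sets the aim: to find out "whether the radiation dose can safely be reduced in trauma patients without compromising the diagnostic accuracy and image quality". The primary outcome is the incidence of delayed diagnoses: "We will estimate the incidence of delayed diagnoses based on a synopsis of all subsequent clinical, imaging, intra-operative, and autopsy findings until discharge". That section also separates clinically relevant delayed diagnoses (severe injuries, or those needing surgical or trans-vascular intervention) from all of them.

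The Analysis plan opens with its criterion: "Accepted statistical methods will be used to determine whether the distribution of baseline variables and outcome results are compatible with chance". The next sentence promises "differences in means and proportions, including appropriate measures of distribution and 95% confidence intervals". Regression for time-series data follows. The Abstract says regression will correct for time and cohort effects, and the Design section foresees an interrupted time-series comparison.

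Under Sample size considerations and calculations, the size is chosen for precision and "not to achieve a certain power to detect an" effect size fixed in advance.

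The only non-inferiority margin in the article is 1 mm on the visual analogue scale. It appears under Design history and IRB concerns and belongs to the abandoned randomised trial, where the endpoint was subjective image quality.

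The Discussion says the non-experimental design cannot formally prove that the low-dose protocol is safe and equally accurate. It then adds: "Advanced statistical approaches will allow for quasi-confirmatory inferences". It closes by saying that the study may supply the best evidence available for choosing between the protocols.

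**The concern.** A claim that accuracy is not compromised needs a statement of how much worse would still be acceptable, and an analysis able to rule out anything larger. A check against chance asks whether zero difference can be rejected. In a study that claims no power for any stated difference, failing to reject zero says little about harm.

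The investigators used the suitable framework for image quality in the abandoned trial, with margin, one-sided alpha and power all stated. When the primary outcome became delayed diagnoses, no counterpart was carried over.

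What is at stake is the meaning of the primary result. An interval that includes both zero and a large increase could be reported as no difference or as inconclusive, and nothing in the plan settles which.

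**Working it through.** **1. The plan's own figure.** For the abandoned trial: margin 1 mm, SD 4 mm, one-sided alpha 0.025, power 80%. n = 2 × (1.96 + 0.8416)² × 4² / 1² = 251.2, so 252 per group; the noncentral t version gives 253 (power 0.7998 at 252, 0.8014 at 253). The stated 253 is reproduced. It concerns image quality and says nothing about delayed diagnoses.

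**2. Inputs for the current design.** From the article: 500 per cohort and 95% intervals, hence a two-sided 5% test. Not in the article, so assumed: the incidence of delayed diagnoses under standard dose, and a true 1.5-fold rise under low dose.

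**3. How often a true 1.5-fold rise is non-significant.** SE = √(p₁q₁/500 + p₂q₂/500); power = Φ(|p₂ − p₁|/SE − 1.96).

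| Assumed true rates | SE | Difference/SE | Power | Non-significant, crude |
|---|---|---|---|---|
| 3% → 4.5% | 0.01201 | 1.249 | Φ(−0.711) = 0.24 | 76% |
| 5% → 7.5% | 0.01529 | 1.635 | Φ(−0.325) = 0.37 | 63% |
| 10% → 15% | 0.02086 | 2.397 | Φ(0.437) = 0.67 | 33% |

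Over a wider range of assumed baselines, power is 17% at 2% and 96% at 20%, so the crude chance of a non-significant result runs from 83% down to 4%.

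**4. With a linear time term.** Take uniform accrual on (0, 1) and a step at 0.5. The covariance of step and time is 3/8 − 1/4 = 1/8; the variances are 1/4 and 1/12. The squared correlation is (1/64)/(1/48) = 0.75, and the variance is multiplied by 1/(1 − 0.75) = 4. SE doubles, so Difference/SE halves:
- 3% → 4.5%: Φ(0.625 − 1.96) = 0.09, non-significant 91%
- 5% → 7.5%: Φ(0.818 − 1.96) = 0.13, non-significant 87%
- 10% → 15%: Φ(1.199 − 1.96) = 0.22, non-significant 78%

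**5. What the promised interval would show.** At an observed 5.0% v 7.5%, the interval is 2.5 ± 1.96 × 1.529 = −0.5 to +5.5 points. It includes zero and also more than a doubling of a 5% rate. Without a stated limit, the plan gives no way to classify it.

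**6. Reading the interval against a margin, at the same size.** A 5-point margin is used for illustration only, with no true difference. Power = Φ(0.05/√(2pq/500) − 1.96).
- 5% incidence: Φ(0.05/0.01378 − 1.96) = Φ(1.667), about 95%; with fourfold variance Φ(1.814 − 1.96), about 44%
- 10% incidence: Φ(0.05/0.01897 − 1.96) = Φ(0.675), about 75%; with fourfold variance Φ(1.318 − 1.96), about 26%

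**7. Why the 5% in the sample size section cannot serve as that margin.** It is a limit on interval width: "95% confidence intervals of both risk and mean differences must not exceed the point estimate by more than 5% in either direction". Used as a harm limit, 5 points would double a 5% rate. It would also pass a true rise from 3% to 4.5% with probability Φ((0.05 − 0.015)/0.01201 − 1.96) = Φ(0.955), about 83% (crude).

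**The case against.** The best defence is that this is an estimation study. The chance sentence is generic and covers baseline variables and outcomes together, differences with 95% intervals follow at once, the size rests on precision, and the Discussion disclaims formal proof. A separate analysis plan might also name a margin. All of that is fair, and it rules out four stronger readings a reader might infer.

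- *The plan treats a non-significant result as proof of safety.* No sentence says so. Safety is also a separate outcome, collected cumulatively.
- *Non-significance is the most likely result whenever low dose is worse.* The documents give no incidence. At a 10% baseline the crude test misses a 1.5-fold rise only 33% of the time, and at 20% only 4%.
- *An observed rise by half would pass unnoticed.* By the chi-square test that is so only at baselines up to about 7%; 50 v 75 cases gives p = 0.017.
- *The review board feared this inferential error.* Its reported concern was the risk of missed injuries to patients in the experimental group.

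What remains does not depend on an unseen document. The article itself states a criterion that does not fit its aim, sets no limit for reading the intervals, and still expects to inform a choice between protocols. The disclaimer of formal proof rests on the lack of randomisation and does not address this gap.

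**Conclusion.** The point holds as a mismatch between aim and criterion. The aim requires ruling out an unacceptable increase in delayed diagnoses, whereas the stated criterion asks only about chance, and the promised intervals have no limit to be read against. A non-significant result could not support a conclusion that diagnosis is uncompromised.

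The size depends on an incidence that the documents do not give. At assumed baselines of 3%, 5% and 10%, a true 1.5-fold rise goes undetected about 76%, 63% and 33% of the time unadjusted. The figures of 91%, 87% and 78% additionally assume a linear time term with uniform accrual in two equal consecutive cohorts. The article commits to time adjustment but not to that exact model.

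**What to change.** In the Analysis plan, remove compatibility with chance as the criterion for outcomes. Before the low-dose cohort starts, state the largest acceptable increase in clinically relevant delayed diagnoses as a risk difference, low dose minus standard dose. Justify it clinically on its own merits and do not borrow it from the 5% precision target.

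Conclude *not compromised* only if the upper limit of the two-sided 95% interval of the adjusted difference lies below that limit. Otherwise report *inconclusive* or *worse*. Limit the Discussion's wording on inference and on choosing between protocols to what this rule can support.

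The cost is one paragraph and no extra patients. The drawback is that some results otherwise described as no difference become inconclusive, and after time adjustment this may happen often: the illustrative powers of 95% and 75% fall to about 44% and 26% under fourfold variance. The plan should say so in advance.

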### Data management and quality assurance

Data management, including data entry, plausibility checks and query generation will be performed by the local trial coordinating unit (Centre of Clinical Research, Unfallkrankenhaus Berlin).

Subjective quality of images, as assessed on 100-mm VAS for general impression and distinct quality of structures, tissues and sites specified earlier, will be graded by two radiologists in a paper-based fashion. Tick-marks on the VAS will be measured and be entered in an electronic data capture (EDC) system by appointed research assistants at the trial unit.

All further data will be handled and stored electronically for further processing, and processed in the database. Data handling and protection will conducted according to GCP and federal laws of data protection.

All materials pertaining to the investigation will be documented by research staff of the trial unit, sorted and kept in closed archives. The investigator should maintain all source data together with related study documentation for the maximum period of time permitted by the hospital, institution or private practice, but not less than that minimally prescribed by the local authorities after the clinical part of the study has been completed.

## Discussion

This is the first study which assesses the potential value of a dose-reducing MDCT regimen in patients with multiple and severe trauma. The investigators initially planned a RCT which was rejected by the local IRB.

The current protocol aims at balancing regulatory and methodological issues. While the present study (because of its non-experimental design) cannot formally prove that low-dose MDCT is feasible, safe, and evenly accurate compared to normal-dose MDCT in the trauma setting, the cohort size, the setting, and the anticipated characteristics of patient cohorts will guarantee both high internal and external validity of findings. Advanced statistical approaches will allow for quasi-confirmatory inferences. In the absence of large-scales RCTs, this study may provide the best available evidence to decide in favour of one or the other diagnostic approach.
